**Methods:**

The proposed feasibility trial is based on a double-blind (outcome assessor and investigators), three-arm (MM usual care, EEG-NF + usual care and usual care control group) randomised controlled parallel clinical trial. Participants with knee OA will be recruited from the community and healthcare practices. A research assistant (RA) will administer both interventions (20-min sessions, four sessions each week, and 12 sessions over three successive weeks). Feasibility measures (participant recruitment rate, adherence to interventions, retention rate), safety, and acceptability of interventions will be recorded. An RA blinded to the group allocation will record secondary outcomes at baseline, immediately post-intervention (4th week), and 3 months post-intervention. The quantitative outcome measures will be descriptively summarised. The qualitative interviews will evaluate the participants' experiences and perceptions regarding various aspects of the trial, which includes identifying the barriers and facilitators in participating in the trial, evaluating their opinions on the research procedures, such as their preferences for the study site, and determining the level of acceptability of the interventions as potential clinical treatments for managing knee OA. Māori participant perceptions of how assessment and training practices could be acceptable to a Māori worldview will be explored. The interviews will be audio-recorded and analysed thematically.

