Both MMT and NF are stand-alone, promising self-regulatory interventions demonstrated to improve pain outcomes. However, evidence of the effectiveness of these two self-regulation training methods is lacking in people with knee OA, a common chronic secondary musculoskeletal pain condition. Although both interventions appear to rely on self-regulatory principles, the physiological and psychological mechanisms through which these two interventions improve pain outcomes may be different (63–69). Therefore, identifying the mechanisms for how these self-regulatory interventions improve outcomes can assist in further optimising protocols to enhance outcomes. Thus, the primary aim of the full clinical trial will be to assess the clinical effectiveness and cost-effectiveness of MMT + usual care and EEG-NF training + usual care against usual care for improving pain and functional outcomes in individuals with knee OA. The secondary aim of the full randomised clinical trial will be to identify the psychological and physiological mechanisms by which training reduces pain and improves function.

However, prior to conducting this full RCT, we propose conducting a feasibility trial to address the factors that could influence the design of the full clinical trial (64). The feasibility issues/questions that require understanding prior to conducting a full-powered RCT are as follows: Are mindfulness meditation and neurofeedback training feasible, safe, and acceptable interventions for people with knee OA? What are the participant recruitment, enrolment, adherence, and dropout rates? What are the adverse side effects of these two self-regulation-based training programmes? What are the participant's experiences of the treatment and research procedures, particularly Māori perceptions of how assessment and training practices in the trial are acceptable to cultural perspectives and values, including Te Ao Māori (a Māori worldview)? What modifications are required for the full trial? What sample size is required to conduct an adequately powered trial?

Therefore, the objectives of this feasibility randomised clinical trial are as follows:

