**Figure 1 F1:**
[figure not shown]
A model wearing an EEG Combi Cap.

We will use the EEG- NF programme administered in our pilot studies in people with chronic musculoskeletal pain, including knee OA (64, 65). Infraslow frequency (<0.1 Hz) is a brain electrical rhythm with maximal spectral power in frequencies below 0.1 Hz. Influencing the ISF may normalise electrical activities across resting-state brain networks that are altered in people with chronic pain (87–90). The pgACC is the chosen region of interest (ROI) for the training due to its connectivity with the periaqueductal grey matter (PAG), which promotes endogenous pain inhibition (17, 90, 91). Up-training ISF at the pgACC improved the pain outcomes in people with chronic pain (65). Therefore, the EEG-NF training programme was designed to up-train the ISF at the pgACC to improve pain outcomes through promoting greater sensory modulation, altering attention and cognitive controllability of pain.

The participants in the control group who are receiving usual care will continue to receive treatments as usual. However, they will refrain from practising meditation during the study period. Following the trial completion, they will be offered to receive one of the trainings.

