Physical function	Knee injury and osteoarthritis outcome score (KOOS): measuring function in daily living (17 items), function in sport and recreation, and knee-related quality of life. Rated on a 5-point ordinal response scale, with anchors of zero (no problems) to 4 (extreme problems).	T_B,_ T_1m,_ T_3m_
Physical activity levels	International physical activity questionnaire—short form in the last 7 days	T_B,_ T_1m,_ T_3m_
Psychological functioning		
Depression, anxiety, and stress	Depression, anxiety, and stress scale (21 items) is a quantitative measure of psychological distress. Rated on scale: 0—never, 1—sometimes, 2—often, 3—almost always.	T_B,_ T_1m,_ T_3m_
State anxiety	The state-trait anxiety inventory will be used to measure state anxiety.	T_B,_ T_1m,_ T_3m_
Pain catastrophising thoughts	Pain catastrophising scale: 13 items; the degree of rumination, magnification, and helplessness when experiencing pain using the 0 (not at all) to 4 (all the time) scale. Total score: 0–52.	T_B,_ T_1m,_ T_3m_
Pain vigilance and awareness behaviour	Pain vigilance and awareness questionnaire (PVAQ): 16 items; the degree of vigilance to and awareness of pain using the 0 (never) to 5 (always) scale. Total score: 0–80.	T_B,_ T_1m,_ T_3m_
Pain self-efficacy	Pain self-efficacy questionnaire (two-item) measures confidence in one's ability to work and lead a normal life despite pain. Rated on 7-point scale: 0 = not at all confident and 6 = completely confident:	T_B,_ T_1m,_ T_3m_
Control of emotions	Emotional regulation questionnaire (10-item scale) measures the tendency to regulate their emotions in two ways: cognitive reappraisal and expressive suppression. Rated on a 7-point ordinal response scale ranging from 1 (strongly disagree), 4 (neutral), to 7 (strongly agree).	T_B,_ T_1m,_ T_3m_
Affect style	Positive and negative affect scale (20 items) Rated on a 5-point ordinal response scale, ranging from 1 = Very slightly or not at all to 5 = Extremely.	T_B,_ T_1m,_ T_3m_
Mindfulness	Five-facet mindfulness questionnaire (15 items) will be used to assess elements of mindfulness. Rated on a 5-point ordinal response scale, ranging from 1 = Never or very rarely true to 5 = Very often or always true.	T_B,_ T_1m,_ T_3m_
Coping levels	A brief pain coping scale will be used to assess coping strategies to manage pain.	T_B,_ T_1m,_ T_3m_
General health and well-being		
Quality of life and well-being	European quality of life-5D and WHO-5 well-being index.	T_B,_ T_1m,_ T_3m_

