### Qualitative study

An assistant research fellow will coordinate with the investigators in conducting semi-structured in-depth interviews following the intervention to evaluate participant experiences in the trial (94, 95). As they finish the trial, the participants will be asked if they would consider this additional interview and be enrolled sequentially until numbers are met. The interview will explore experiences and perceptions regarding interventions based on the theoretical framework of acceptability. These would be recorded with the consent of the participants. The aims of this interview include exploring the participants’ experiences regarding the barriers and facilitators in participating in the trial. In addition, the interview aims to assess the acceptability of the research procedures, including the intervention, preferences for the study site, the perceived value of the study, and the acceptability of interventions as potential clinical treatments for managing knee OA. Furthermore, the interview seeks to explore the perspectives of Māori people on assessment and treatment practices that align with their cultural worldview (95). Māori is treated as an important subgroup and are selected and interviewed separately. We aim to interview five people per group with a purposeful sample of Māori participants from each group. The participants in the usual care group will also be interviewed to explore their experiences participating in the trial, including the acceptability of the assessment procedures.

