### Outcome assessor and blinding

A research assistant who will be blinded to the groups will collect the secondary outcomes at baseline, immediately post-intervention, and 3 months post-intervention. The effectiveness of blinding will be measured. The self-report questionnaires will be administered using the Qualtrics data management system. The participants will complete the questionnaires in two parts: at home and in person during the assessment sessions.

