The conditioned pain modulation (CPM) procedure will be administered according to the published recommendations (98, 115) to measure the efficiency of the endogenous pain modulatory system. The conditioning stimulus involves the participants submerging their dominant hand in a cold water (−5°) bath for 2 min (maximum period) or until it is too uncomfortable. Pain intensity during the conditioning stimulus will be recorded on a 11-point NPRS (0 = no pain to 100 = extreme pain) at every 15 s intervals (98). The test stimulus involves measuring the suprathreshold PPT (pain40) at the tibialis anterior muscle over the non-dominant leg region. Two PPT (pain40) trials prior to exposure to the conditioning stimulus and three trials of PPT (pain40) trials at 30, 60, and 90 s following the conditioning stimulus will be recorded. The CPM will be determined by calculating the percent change score for each time point. Heart rate and blood pressure will be monitored for safety reasons.

For the collection, processing, and analysis of EEG data (125–127), the SynAmps RT Amplifier (Compudemics Neuroscan) will be used to capture resting-state EEG data for 10 min while the participant is seated in an upright position in a quiet room with closed eyes. The raw EEG signals will be processed according to our previous work (125–127). Exact low-resolution brain electromagnetic tomography (eLORETA) software will be used to estimate the intracerebral electrical sources in the following frequency bands: infraslow (0.01–0.10 Hz), slow (0.2–1.5 Hz), delta (2–3.5 Hz), theta (4–7.5 Hz), alpha1 (8–10 Hz), alpha2 (10.5–12 Hz), beta1 (12.5–18 Hz), beta2 (18.5–21 Hz), beta3 (21.5–30 Hz), and gamma (30.5–44 Hz). The current source density (CSD) and functional connectivity (FC) will be calculated for the selected regions of interest (ROIs), namely, pregenual, sub-genual, prefrontal, cingulate, insular, and somatosensory cortices. MM and NF interventions have been studied previously and have demonstrated altering the activity of the ROIs chosen in this trial. The changes in the CSD of the selected ROIs and FC between ROIs will be analysed within and between groups.

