## Quantitative data analyses plan

Descriptive statistics will be derived for primary and secondary outcome measures. The sample size estimation was not determined for primary outcomes since it is a feasibility trial. However, we aim to recruit a sample (20 participants per group, 60 in total) in 1 year in a single centre to provide sufficient data for assessing adverse events, feasibility outcomes, identifying operational issues, and estimating variability estimates of clinical pain outcomes.

**In the full clinical trial**, linear mixed models will be used to examine the differences in changes in the pain and physical function between groups to determine the effectiveness of interventions against usual care based on the randomised group (i.e., using an intention-to-treat approach). Group–time interactions will be used to assess between-group differences at 1 and 3 months following the intervention, with 3 months being the primary endpoint. Potential explanatory factors (which could include age, sex, BMI, duration, baseline pain severity, and depression scores) will be adjusted in the analysis. In this feasibility study, we will still perform these analyses (with no stratification or competing exposure variables included) to assess the study protocol, focusing on the uncertainty in estimated effects, not statistical significance. The following parameters will be used to determine the sample size in the full clinical trial: standard deviations (SD) and correlations between repeated measures of outcome measures derived from the feasibility trial. The full trial will have 80% power to detect a meaningful difference in the primary outcome (i.e., pain severity at 3 months). The minimal clinically important difference for pain severity (NPRS) is 1.8 using a two-sided (0.05) significance level. An attrition rate informed by the results of this feasibility study will be incorporated.

Qualitative data analysis (72): The interviews will be audio-recorded and fully transcribed. The General Inductive Approach will guide the analysis. The qualitative findings will provide important information regarding recruitment and retention in the trial and the acceptability of interventions. The results of the qualitative study will be published separately.

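### As printed, only the usual-care arm is told to refrain from meditation; no matching rule is stated for the EEG-NF arm it is compared with

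*Protocol article*

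**What the plan says.** The rule is in the last paragraph of the EEG-NF training section, after Figure 1. That paragraph concerns the control group: they carry on with their treatments, but "they will refrain from practising meditation during the study period". The Allocation concealment section also describes what controls are told (manage the condition as usual, attend follow-up) and does not mention meditation.

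The arms are set out in the Methods part of the abstract: "three-arm (MM usual care, EEG-NF + usual care and usual care control group". The Introduction gives the full trial's contrast for this arm as "EEG-NF training + usual care against usual care", with a parallel contrast for mindfulness.

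The contrast is also estimated in the present study. After describing the between-group mixed models for pain and function, the Quantitative data analyses plan says: "In this feasibility study, we will still perform these analyses". The EEG paragraph, under Cardiovascular measures, says that changes in source density and connectivity "will be analysed within and between groups".

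**The concern.** In an add-on design, usual care is the common background and the randomised training is the only intended difference. A co-intervention rule stated for one side of that contrast breaks this. Read literally, controls receive usual care without meditation, while nothing stated stops EEG-NF participants from meditating.

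The likely purpose of the rule is to keep controls from giving themselves the content of the mindfulness arm. The same reason applies to EEG-NF participants, who are unblinded and know they are in a trial that tests mindfulness. If outside meditation helps and some of them practise it, EEG-NF versus usual care is tilted towards EEG-NF, and EEG-NF versus mindfulness becomes less distinct. The EEG outcomes could be touched as well, since the article says both trainings have been shown to alter activity in the chosen brain regions.

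The Introduction asks what should be modified for the full trial. A one-sided rule is best corrected before that trial inherits it.

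**Working it through.** **1. Who the rule covers.** The subject of the sentence is the control group. It sits under the EEG-NF heading, but nothing in the paragraph extends it to EEG-NF participants.

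**2. Whether another section states it for EEG-NF.**
- Table 1 (intervention description) and EEG-NF training: conduct within sessions only, such as posture, closed eyes and limiting movement.
- Interventions: session number and length only.
- Study eligibility criteria: people who already meditate are not excluded.

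The article therefore states the rule for one arm only.

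**3. What the planned measures would show about outside practice.**
- Baseline assessment: other pain-management treatments are recorded, which may include meditation, but this is a baseline item.
- Table 2, three time points: "Five-facet mindfulness questionnaire (15 items) will be used to assess elements of mindfulness". These are elements of mindfulness, not practice outside the trial, and either training might change them.
- Table 2, coping scale (three time points) and cost questionnaire (baseline and 3 months): each may capture part of it. The items are not shown, and free home practice may not appear as healthcare use or expense.
- Qualitative study: "We aim to interview five people per group", that is 5 of a planned 20, or 25% of each arm.

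This is indirect cover, but it is not nil.

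**4. Size, for illustration only.** The article gives no uptake figure and no SD. From it come the 1.8-point minimal clinically important difference, 20 per arm and the 80% retention target (20 × 0.80 = 16). Assumed: a net between-arm difference in outside meditation p = 0.10 to 0.20 (2 to 4 of 20), a benefit d = 0.9 to 1.8 points (half to all of 1.8), and SD 2.0 to 2.5.

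Shift = p × d:
- lowest: 0.10 × 0.9 = 0.09 points
- highest: 0.20 × 1.8 = 0.36 points

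95% half-width for a simple two-arm difference in means = t × SD × √(2/n):

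| n per arm | t | SD 2.0 | SD 2.5 |
|---|---|---|---|
| 20 | 2.024 (38 df) | 1.28 | 1.60 |
| 16 | 2.042 (30 df) | 1.44 | 1.81 |

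Shift relative to half-width: lowest 0.09/1.805 = 5%, highest 0.36/1.280 = 28%.

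**5. Effect on the SD carried forward.** If only the EEG-NF arm contains such practice, its variance rises by p(1 − p)d²:
- lowest: 0.10 × 0.90 × 0.81 = 0.073
- highest: 0.20 × 0.80 × 3.24 = 0.518

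Pooled over three equal arms, SD becomes √(SD² + extra/3):
- SD 2.0 becomes 2.006 to 2.043 (+0.3% to +2.1%)
- SD 2.5 becomes 2.505 to 2.534 (+0.2% to +1.4%)

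**The case against.** The strongest reply is that this is a condensed article. What each arm is told about activities outside sessions normally sits in the full protocol and information sheet, which are not shown and may already extend the rule. That stands as a limit. A reader might infer that EEG-NF participants are free to meditate, or are told so, and the article does not say this. It does, however, print a rule for one side of a contrast it estimates, which is more than leaving the topic to a fuller document.

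The second reply is that no decision in this study turns on it, and this also largely stands. The primary outcomes are recruitment, compliance, retention and safety. The full trial's sample size uses SDs, correlations and attrition with a fixed 1.8-point difference, not the observed effect. The between-group models are read for uncertainty, not significance.

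Third, a reader might infer that the study would be blind to differences in outside practice. The documents do not support that: other treatments, mindfulness, coping, costs and interviews all bear on it. What is missing from the description is a direct measure.

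Fourth, the illustration rests on assumed inputs. Its upper end needs the largest uptake difference, the full benefit, the smallest SD and no dropout together. The half-widths are also not those of the planned mixed model. The figures show the order of size and are not evidence of bias.

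**Conclusion.** The point holds in a limited form and is minor. As printed, a co-intervention rule applies to usual care and not to EEG-NF. If that is how the trial is run, background care differs by arm after randomisation. The direction of any tilt depends on meditation helping and on some EEG-NF participants practising it, and its size cannot be derived from the article. On the stated assumptions it is small beside the imprecision expected at 16 to 20 per arm, and the pooled SD moves by about 2% at most.

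It would go too far to conclude that the feasibility findings or the inputs to the full trial's sample size are compromised. What is affected is the reading of the descriptive EEG-NF contrasts and the design handed on to the full trial.

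**What to change.** Give EEG-NF participants the same instruction to refrain from outside meditation during the study as usual-care participants.

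Add one item on meditation practice outside the trial (yes/no, minutes per week) in all three arms at baseline, week 4 and 3 months. The means already exist: "The self-report questionnaires will be administered using the Qualtrics data management system". Since those questionnaires are completed partly at home and partly in person, put the item in the home part and keep the answers from the blinded assessor, because they could reveal the group.

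The cost is one line in the information sheet and one short question at three time points, on top of a questionnaire load that the Discussion already acknowledges. The real downside is an added restriction for EEG-NF participants, including any who already meditate, which moves their background slightly away from true usual care. Controls already carry that restriction. Dropping it for controls would also restore symmetry, but would leave both arms free to take up the mindfulness arm's content.

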### Outcome measures

The assistant research fellow will collect primary outcome measures throughout the study period. All secondary outcome measures will be collected at baseline, immediately post-intervention (4th week), and 3 months post-intervention by a research assistant (RA-2) blinded to group allocation. The RA will be adequately trained to collect quantitative sensory testing procedures, electrocardiogram, and electroencephalography recordings (Table 2).

**Table 2 T2:** Secondary outcome measures.

Outcome domain and constructs (96–98)	Brief description of measurement tools	Measurement time points
Pain		
Pain severity	The brief pain inventory—short form (pain subscale) Pain severity on a 10-point scale (0 = no pain and 10 = worst pain possible) in the past 24 h, 1 week, and 4 weeks.	T_B,_ T_1m,_ T_3m_
Pain unpleasantness	In the last 2 weeks, how unpleasant has your knee pain been? ‘Not at all’, ‘slightly’, ‘moderately’, ‘very much’, and ‘extremely’.	T_B,_ T_1m,_ T_3m_
Pain bothersomeness	In the last 2 weeks, how bothersome has your knee pain been? ‘Not at all’, ‘slightly’, ‘moderately’, ‘very much’, and ‘extremely’.	T_B,_ T_1m,_ T_3m_
Intermittent and constant pain	The measure of intermittent and constant osteoarthritis pain (11 items). Each item is rated on a 5-point ordinal response scale (Not at all/No constant or intermittent knee pain, Mildly, Moderately, Severely, Extremely).	T_B,_ T_1m,_ T_3m_
Pain quality	PainDETECT questionnaire (12 items). Each symptom is rated on a 5-point ordinal response scale (1 = never to 5 = very strongly). Score classification: ≤12—nociceptive pain, 13–18—possible neuropathic pain, ≥19—likely neuropathic pain.	T_B,_ T_1m,_ T_3m_
Movement evoked pain	Pain severity during a 6-min walk distance and physical performance tasks—rated pain on NPRS on a 0–100 scale (0 = no pain, 100 = the most intense pain imaginable) scale.	T_B,_ T_1m,_ T_3m_
Flare in osteoarthritis	Flare-OA (16 items) patient-reported instrument to assess the occurrence and severity of knee OA in the past 4 weeks.	T_B,_ T_1m,_ T_3m_
Physical functioning		
Pain interference	The brief pain inventory—short form (interference subscale—nine items) evaluate the impact of pain on daily activities Rated on a 10-point scale (0 = no pain and 10 = worst pain possible).	T_B,_ T_1m,_ T_3m_
Physical function	Knee injury and osteoarthritis outcome score (KOOS): measuring function in daily living (17 items), function in sport and recreation, and knee-related quality of life. Rated on a 5-point ordinal response scale, with anchors of zero (no problems) to 4 (extreme problems).	T_B,_ T_1m,_ T_3m_
Physical activity levels	International physical activity questionnaire—short form in the last 7 days	T_B,_ T_1m,_ T_3m_
Psychological functioning		
Depression, anxiety, and stress	Depression, anxiety, and stress scale (21 items) is a quantitative measure of psychological distress. Rated on scale: 0—never, 1—sometimes, 2—often, 3—almost always.	T_B,_ T_1m,_ T_3m_
State anxiety	The state-trait anxiety inventory will be used to measure state anxiety.	T_B,_ T_1m,_ T_3m_
Pain catastrophising thoughts	Pain catastrophising scale: 13 items; the degree of rumination, magnification, and helplessness when experiencing pain using the 0 (not at all) to 4 (all the time) scale. Total score: 0–52.	T_B,_ T_1m,_ T_3m_
Pain vigilance and awareness behaviour	Pain vigilance and awareness questionnaire (PVAQ): 16 items; the degree of vigilance to and awareness of pain using the 0 (never) to 5 (always) scale. Total score: 0–80.	T_B,_ T_1m,_ T_3m_
Pain self-efficacy	Pain self-efficacy questionnaire (two-item) measures confidence in one's ability to work and lead a normal life despite pain. Rated on 7-point scale: 0 = not at all confident and 6 = completely confident:	T_B,_ T_1m,_ T_3m_
Control of emotions	Emotional regulation questionnaire (10-item scale) measures the tendency to regulate their emotions in two ways: cognitive reappraisal and expressive suppression. Rated on a 7-point ordinal response scale ranging from 1 (strongly disagree), 4 (neutral), to 7 (strongly agree).	T_B,_ T_1m,_ T_3m_
Affect style	Positive and negative affect scale (20 items) Rated on a 5-point ordinal response scale, ranging from 1 = Very slightly or not at all to 5 = Extremely.	T_B,_ T_1m,_ T_3m_
Mindfulness	Five-facet mindfulness questionnaire (15 items) will be used to assess elements of mindfulness. Rated on a 5-point ordinal response scale, ranging from 1 = Never or very rarely true to 5 = Very often or always true.	T_B,_ T_1m,_ T_3m_
Coping levels	A brief pain coping scale will be used to assess coping strategies to manage pain.	T_B,_ T_1m,_ T_3m_
General health and well-being		
Quality of life and well-being	European quality of life-5D and WHO-5 well-being index.	T_B,_ T_1m,_ T_3m_
Sleep quality and disturbances	Pittsburgh sleep quality index (19 items) assesses sleep quality over a 1-month time interval. Scored 0 (no difficulty) to 3 (severe difficulty). Total score (range 0–21). Higher scores indicate worse sleep quality.	T_B,_ T_1m,_ T_3m_
The participants’ perceptions about interventions and their impact on their health condition/pain.		
Global perceived change	Perceived change in the knee pain when compared to baseline/before training (−5 = much worse, through 0 = unchanged, to +5 = completely, recovered).	T_1m, and_ T_3m_
Acceptability of interventions	Visual analogue scales (0–10) to measure overall acceptability, burden, perceived effectiveness, ethicality, culturally acceptable, research team's trustworthiness and knowledge, and the likelihood of negative side effects of training.	T_B_
Perceived treatment satisfaction and usefulness of training	Rated on a 0–10 NRS; 0—not at all satisfied to 10—highly satisfied.	T1m, and T3m
Credibility/expectancy of the intervention	The credibility/expectancy questionnaire (5 items)	T_B_
Predictors of training		
Level of engagement with the training	Rated on a 10-point ordinal items scale, where 1 = least engaged and 10 = highly engaged.	At every session
Level of motivation	Single-item; rated on a 10-point ordinal items scale, where 1 = least motivated and 10 = highly motivated.	T_B_ and every session
Cost-and-consequences		
Costs	The osteoarthritis cost-and-consequences questionnaire will be used to measure healthcare use/expenses in the past 3 months.	T_B,_ and T_3m_
Quantitative sensory testing, physical performance assessment and physiological recordings		
	Quantitative sensory testing procedures	T_B,_ T_1m,_ T_3m_
	Resting and evoked electroencephalography.	
	Heart rate, blood pressure, and respiratory rates	
	OARSI Minimum physical performance core set	
	Short physical performance battery (SPPB) standing balance tasks.	

T_B_, at baseline; T_1m_, immediately post-intervention (4th week); T_3m_, 3 months post-intervention.

